##### Selecting and titrating appropriate exposure tasks

After individualizing their fear hierarchies, therapists were asked to select a starting task from the list that felt like a “challenging but doable” scenario. The trainer emphasized the importance of selecting an item that brings up at least some anxiety in order for therapists to experience the true process of exposure for themselves. After the first self-exposure trial, therapists were given the option to repeat the same exposure or modify the challenge level to be harder or easier in their second round of self-exposure. After completing a second self-exposure, therapists partnered up and took turns playing the role of patient or therapist. Those in the patient role discussed the recent self-exposure they had conducted and those in the therapist role helped their partner select and titrate their next exposure task.

##### Conducting exposures in a prolonged and intense manner

Before engaging in each exposure task, therapists were instructed to persist with their exposure task past the point at which they assumed a negative outcome would occur or past the point at which they would be inclined to stop; these instructions align with theories of optimal exposure delivery for promoting new learning about the dangerousness and tolerability of their feared situation (58, 59). Therapists were given up to 5 min to complete each round of self-exposure and 8 min to complete each partner exposure; these durations were selected to allow enough time for individuals to thoroughly approach their feared item/situation while also keeping the exposure window brief enough to allow for repeated trials. Therapists were guided to select exposure tasks that could be completed within the window and allow enough time for safety learning and habituation to occur (e.g., singing to the group). This was plenty of time for most participants to fully engage with feared content and experience new safety learning.

##### Consolidating learning

Before each self-exposure task, therapists discussed which task they were attempting, their anticipatory anxiety level, and the feared outcome they were testing. Then, after completing their self-exposure, they returned to the group and reported their overall experience during the exposure and their revised estimates of the dangerousness and/or intolerability of their exposure task. A similar process took place during partner exposures for the individual in the patient role, except that those in the therapist role also reported on their experience, anxiety levels, and what they learned while directing someone else’s exposure experience. The goal of the pre-and post-processing was to practice this important element of actual exposure delivery and to witness the accumulation of new safety learning among all group members in both the patient and provider roles.

#### Phase 2: Randomized training trial (ongoing)

Therapists were randomly assigned to either a didactic-only or a didactic plus E2E training workshop which was 12 h in total. All therapists completed the same 8-h “Core Workshop,” which was followed by a condition-specific 4-h training (Didactic or E2E). Following the workshop training, therapists began using exposure therapy with patients presenting with anxiety disorders and received ongoing weekly consultation. Each therapist was encouraged to refer 1–2 patients to the study to receive ongoing consultation regarding the use of exposure therapy for patients who elected to participate in the study. In line with the gold-standard structure for therapist training, therapists with enrolled patients attended weekly, hour-long consultation conducted in a group format *via* video teleconferencing.

##### Core workshop

This was a didactic training that covered foundational information about anxiety disorders, maintenance theories and the principles of exposure delivery, including: (a) a diagnostic overview of common anxiety disorders including OCD, (b) developmental considerations, (c) presentation of the CBT model of anxiety, (d) a functional explanation of anxiety symptoms and their maintenance, (e) an introduction to four main components of exposure therapy (psychoeducation, hierarchy development, exposure tasks, and relapse prevention), (f) an in-depth discussion of the procedures for conducting each component of exposure therapy, (g) advice for troubleshooting common issues when delivering exposure therapy, (h) and a discussion of considerations for delivering exposure therapy in the home setting.

##### Didactic condition

Those in the didactic condition reviewed key concepts from the prior 8-h training, including the CBT model of anxiety maintenance, the rationale for how exposure directly counteracts the maintenance model, and principles for conducting optimal exposure tasks. Therapists in this condition also spent extra time reflecting on their own caseloads and discussing current (or past) patients that might be a good fit for exposure to assist with the process of identifying eligible patient participants.

##### Exposure to exposure (E2E) condition

Those in the E2E training condition briefly reviewed previous didactic content (1 h), before engaging in experiential training strategies. Experiential activities followed the steps of (1) generating a fear hierarchy, (2) selecting and titrating appropriate exposure tasks, (3) conducting exposure in a prolonged and intense manner, and (4) consolidating learning as described in the “Optimizing E2E” section above. After completing two rounds of self-exposure all therapists completed the BES-T. Regardless of whether they selected “No More Practice – I am Ready” on the BES-T go/no-go item, all therapists then completed two rounds of partner exposures. After two rounds of partner exposures they again completed the BES-T, and those who endorsed “No More Practice – I am Ready” were placed in a waiting room to discuss their current patient caseload and think about potential patient referrals to the study, while those endorsing “Not Yet” completed another round of partner exposure with a study confederate (research assistant) in either the patient or provider role depending on which they thought would be most helpful for increasing their exposure confidence; in all instances, those requiring additional practice elected to be in the therapist role. Therapists repeated the partner exposure task and completed the BES-T after each trial until they selected “No More Practice – I am Ready.”

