### Applying a mechanistic framework to the design and testing of training interventions

Experimental therapeutics is a mechanism-testing framework promoted by the National Institute of Health (NIH) Science of Behavior Change (46) and the National Institute of Mental Health [NIMH; (47, 48)] to support the rigorous evaluation of candidate change mechanisms as a more efficient means to intervention development. Perhaps because of its roots with novel biological interventions and targets, it has been applied infrequently in the development of novel service interventions, despite explicit calls to do so (48, 49). The experimental therapeutics framework goes beyond asking whether or not an intervention works to clarify how and why the intervention works. The broad goals of this approach are: (1) to select a target mechanism with preliminary evidence demonstrating malleability to the proposed intervention, and (2) to demonstrate that change in the target also affects planned outcomes. More rigorous applications of experimental therapeutics should aim to demonstrate a causal dose–response relationship between the intervention, target mechanism, and planned outcomes. As indicated in Figure 2, the progression of the present investigation is designed to fit the experimental therapeutics model.

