#### Measurement considerations

While piloting measure administration during the case-series in Phase 1 it became clear that repeatedly administering the TBES after rounds of the experiential tasks was burdensome, interrupted the learning flow, and posed a potential risk of sampling error. This led to the development of the brief BES-T measure to allow for frequent monitoring of change in the belief target without interrupting training and potentially undermining the potency of experiential learning. During the case-series analysis, therapists who endorsed feeling ready to use exposure on the BES-T go/no-go item (4 of 6 therapists) following E2E procedures also reported post-workshop TBES scores below the *a-priori* criterion score, while those who endorsed not yet feeling ready to use exposure (2 of 6 therapists) were above the TBES criterion score at post-workshop. It is possible therapists could simply endorse feeling ready to use exposure to end experiential training tasks, but the consistency between endorsement of this item with our TBES clinical criterion score would suggest therapists answered truthfully in the Phase 1 case-series. Future measurement strategies will take into closer consideration the possibility of therapists potentially endorsing a willingness to use exposure in order to discontinue experiential activities. The sixth item in the BES-T measure is also a double-barreled question assessing both therapists’ confidence and intent to use exposure that will likely need to be broken out into two separate questions in a future test of the E2E training intervention. At present, it is possible a therapist could be confident but still not intend to use exposure and the current question configuration would not allow sensitivity to this possibility. Resulting finding will be interpreted in light of this consideration. Time points for sampling therapist beliefs were carefully chosen to allow for mechanism evaluation. As depicted in Figure 3, the intervention target was assessed before, during, and after the experimental E2E training strategies were implemented. An easy to administer process measure for assessing incremental change in the belief target was also implemented during experiential E2E training tasks to measure dose response, and a rigorous micro-analytic coding system was used to quantify the outcome of interest (i.e., therapist delivery behavior; Table 1).

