**Figure 3 fig3:**
[figure not shown]
Training activities, hypotheses, and measurement strategy. EBPAS = Evidence Based Practice Attitudes Scale; TBES = Therapist negative Beliefs about Exposure.

**Table 1 tab1:** Measurement strategy and timepoints.

Measure (*Objective*)	Timepoint					
	Baseline	End of core didactics	During experiential (E2E only)	End of workshop	Consult	End of study
TBES (*Primary target*)	X	X		X		X
EBPAS (*Target specificity*)	X	X		X		X
Knowledge (*Candidate target*)	X	X		X		X
Self-efficacy (*Candidate target*)	X	X		X		X
BES-T (*Target process*)			X			
Training satisfaction (*QI*)				X		X
EPCS (*Outcome*)					X	

BES-T = Beliefs about Exposure Scale – Training; EBPAS = Evidence Based Practice Attitudes Scale; EPCS = Exposure Process Coding System; Knowledge = Exposure Knowledge Measure; Self-Efficacy = Measure of Exposure Delivery Self-efficacy; TBES = Therapist negative Beliefs about Exposure; Training Satisfaction = Training Acceptability Rating Scale (TARS).

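### The BES-T schedule cannot support a causal dose-response; it describes incremental change after self-exposure only

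*Protocol article*

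**What the plan says.** Under Measurement considerations, the article says a short process measure "was also implemented during experiential E2E training tasks to measure dose response". The same section says that "the intervention target was assessed before, during, and after the experimental E2E training strategies were implemented". The section on the mechanistic framework states that more rigorous applications "should aim to demonstrate a causal dose–response relationship between the intervention, target mechanism, and planned outcomes".

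The schedule is under Exposure to exposure (E2E) condition. "After completing two rounds of self-exposure all therapists completed the BES-T". Whatever they answered on the readiness item, "all therapists then completed two rounds of partner exposures" and then the BES-T again. Those who declared themselves ready stopped. The others went on: "Therapists repeated the partner exposure task and completed the BES-T after each trial until they selected" the ready option. Table 1 marks the BES-T at one point only, during the experiential part and in the E2E arm alone. It marks the TBES, the primary target measure, at baseline, end of core didactics, end of workshop and end of study.

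**The concern.** A dose-response needs a reading at zero dose or a comparator, and differences in dose that the response itself does not produce. The BES-T has neither. Self-exposure is one of the two E2E strategies, and it is finished before the first BES-T is taken. Up to round four all E2E therapists have the same dose. After that the dose differs only because some therapists said they were not yet ready.

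What is at stake is interpretation. A published statement that the BES-T showed a dose-response would read as mechanistic evidence that this design cannot give. A table of beliefs by number of rounds would mainly sort therapists by how reluctant they were or how slowly they changed.

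**Working it through.** The plan gives no figure to reproduce here. The check sets the schedule beside the claim, then works out what the readings can identify.

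**1. Readings against rounds** (E2E condition section and Table 1)

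| Point | Rounds done | BES-T, E2E arm | BES-T, didactic arm | Dose set by |
|---|---|---|---|---|
| Before first task | 0 | none | none | – |
| After self-exposures | 2 | all | none | design |
| After partner exposures | 4 | all | none | design |
| Each later round | 5 or more | those not ready | none | own readiness answer |

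**2. What the fixed step identifies.** Let B be the belief before the tasks (higher is worse), s the fall per self-exposure round, p the fall per partner round, and t the fall per round-length of time from any other cause, including repeat testing. The expected readings are:

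- after round 2: B − 2s − 2t
- after round 4: B − 2s − 2p − 4t
- difference: 2p + 2t

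The self-exposure effect s cancels, so the BES-T carries no information on it without a start value. The partner effect p cannot be separated from t without a comparator.

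A simulation of the schedule shows the same. Its inputs are assumptions, not document figures: 18 E2E therapists (arm sizes are not given), start mean 50, SD 20, error SD 8, ready at 30 or below, at most 10 extra rounds, 4,000 runs.

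- A true effect of 5 per round with no time trend gives an expected step of 2 × 5 = 10 (simulated 9.98). Mean fall from start to last reading: 32.4.
- No round effect, but a time trend of 5 per round-length, gives an expected step of 2 × 5 = 10 (simulated 10.04). Mean fall: 32.3. The two cannot be told apart.
- A 20-point fall wholly before the first reading gives an expected step of 0 (simulated 0.04).

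**3. What happens if rounds are used as the dose.** Same inputs:

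- True effect zero: final belief rises 4.4 points per extra round. The round-4 score, taken before any extra round, already rises 3.8 per extra round. The association comes from who continues.
- True effect 5 per round: final belief still rises 1.8 points per extra round.

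A second set of assumed inputs: 18 therapists, start mean 50, SD 15, fall per round mean 6 and SD 2.5 between therapists, error SD 5, stop at 30 or below once four rounds are done, at most 12 rounds, 3,000 runs. About 41% to 42% go beyond four rounds. Ranges are over repeated runs.

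| Rounds correlated with | r |
|---|---|
| Final negative belief | +0.55 to +0.59 |
| Benefit per round | -0.53 |
| Total reduction | +0.11 to +0.13 |
| Reduction visible on the BES-T, first to last reading | +0.38 to +0.39 |

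With the mean fall per round at about 0, 3, 6 or 9 and the readiness threshold at 20, 30 or 40, the first correlation stayed positive in all twelve settings (+0.46 to +0.80, give or take a few hundredths with coding detail). The second stayed negative (-0.32 to -0.66). The other two are not stable in sign: varying one input at a time, total reduction ran from -0.21 to +1.0 and visible reduction from -0.06 to +0.73.

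**4. Where the BES-T enters the stated analyses.** Under Anticipated results, Hypothesis 1 uses the TBES, Hypothesis 2 the TBES and EBPAS, Hypothesis 3 the EPCS against TBES, and Hypothesis 4 exposure utilization against negative beliefs. None uses the BES-T or a count of rounds.

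**The case against.** The strongest reply is that nobody plans the faulty analysis. No regression on rounds is stated, and the article also describes the BES-T as tracking incremental change, which is a within-therapist description. How it would be analysed may sit in a fuller document. This stands, and it limits the point to the stated purpose of the measure. It does not remove the point, because no later analysis plan can supply a reading that was not scheduled.

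Second, the framework section ties dose-response only to more rigorous applications, and the Discussion names target engagement and the target-outcome relationship as the assumptions this pilot tests. This also stands: the mechanism case as a whole does not rest on dose-response.

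Third, the step from round 2 to round 4 is free of the stopping rule, and readiness is a separate item from the five belief ratings. Both are correct. That step is usable as description, and the simulated cut at 30 is only a stand-in for the readiness answer.

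A reader might infer that the statement about assessment before, during and after E2E is false. It is not. It concerns the target, and Table 1 has the TBES on both sides of the E2E tasks. A reader might also infer that a rounds analysis would always make E2E look harmful. The table above does not support that: the sign depends on the outcome and on the inputs.

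**Conclusion.** The point holds as a limit on what the BES-T can show. The schedule and the stated purpose do not fit: there is no zero-dose reading, no comparator reading, no variation in dose through round four, and response-driven dose after that. The article discloses two weaknesses of the readiness item (insincere answers and double-barreled wording) but neither of these. The BES-T can describe change within therapists after self-exposure. It cannot support a causal dose-response.

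The impact is moderate. Hypotheses 1 to 4 and the primary comparison are untouched. That rounds would be confounded by response follows from the schedule alone. The size and sign of any resulting association rest on assumed inputs and should be read as illustration.

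**What to change.** - Under Measurement considerations, replace the dose-response purpose with a statement that the BES-T describes within-therapist incremental change from after self-exposure onward.
- Do not analyse or interpret the number of rounds as a dose. It may be reported as a description of how much practice therapists took before declaring themselves ready.
- Estimate the E2E-specific effect by comparing the arms on the TBES from end of core didactics to end of workshop. This spans the condition-specific four hours, is already collected in both arms, and sits beside Hypothesis 1 without altering it.

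The cost is a change of wording and one added comparison on existing data. The downside is that the dose-response claim is given up for this trial. All 36 Phase 2 therapists have completed the workshop, so a BES-T reading before the first task, with matched readings in the didactic arm, applies only to any further workshop. There, the five belief items would take a minute or two.

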##### Supervision

Following the initial workshop, therapists delivered exposure therapy with patients recruited to the study and attended weekly (60-min), condition-specific consultation meetings. All supervision took place remotely *via* Zoom. The general format of supervision included: (1) triage of any urgent patient matters, (2) allocation of extra time for therapists starting a new exposure case, and (3) rotation of the order in which therapists presented their cases to ensure equal time and focus. Supervision in the didactic condition focused on principles and procedures of exposure delivery, including troubleshooting of exposure delivery barriers, but avoided conversation about therapist anxiety and the E2E concept. Supervision in the E2E condition had a similar focus on delivery principles and troubleshooting but also prioritized each therapists’ processing of negative beliefs. Specifically, therapists were asked what negative beliefs they planned to test in their upcoming exposure sessions and they were asked to reflect on what they learned about their negative beliefs in the subsequent supervision session. Supervision in the E2E condition was the same duration and frequency as the didactic condition, as additional discussion of negative beliefs required minimal extra time or focus when embedded within the larger conversation. All supervision sessions were audio recorded to allow for fidelity monitoring.

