## Anticipated results

The primary goals of this study are to first establish and then confirm engagement of the negative beliefs target with the novel E2E training approach, and to also demonstrate a relationship between change in the beliefs target and therapists’ in-session delivery behaviors. Target engagement was established during the Phase 1 trial. The Phase 2 training trial will confirm target engagement by demonstrating significantly greater change in belief scores following workshop training for therapists assigned to E2E relative to the didactic group (Hypothesis 1). To test this effect, group status (E2E vs. didactic) will be entered as a predictor of post-workshop total TBES score while including a random intercept for TBES baseline score. It is anticipated that as TBES-measured belief levels approach zero, the distribution will become positively skewed. This is problematic given the goal to target and reduce belief levels as close to zero as possible. To account for the positive skew of TBES scores approaching zero, binomial-based modeling will be used to conduct a logistic regression to assess for a difference in belief reduction between those in the didactic and E2E groups following the workshop training. Figure 3 illustrates the measurement time points and pathways for testing planned hypotheses.

It is also expected that the E2E intervention will produce a specific change in negative beliefs (measured pre-and post-workshop) about exposure but not differentially affect broader beliefs about EBPs (EBPAS) in general (Hypothesis 2). Target specificity will be demonstrated by significantly greater levels of negative belief change but comparable levels of EBP belief change in the E2E group relative to didactic. The pilot nature of this study does not allow sufficient statistical power to conduct a non-inferiority test of group differences on EBPAS change, so comparison of descriptive statistics will provide initial evidence of specificity to be fully tested in a larger trial (61, 62).

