The relationship between target change (i.e., reduction in negative beliefs) and outcomes of interest will be evaluated using the EPCS micro-analytic coding system for categorizing in-session exposure delivery behavior (Hypothesis 3). Therapist delivery behaviors during the consultation phase of training will be categorized into “optimal” (i.e., delivery behaviors intended to engage and intensify patient anxiety) and “suboptimal” (i.e., delivery behaviors intended to artificially reduce patient anxiety) categories in accordance with previously established procedures (54). Rates of optimal and suboptimal delivery behaviors will be calculated for each therapist with recorded session data, and in-session behavior will be examined as a function of post-training TBES scores using GLM (Gaussian distribution); these will be conducted as two separate tests examining optimal and suboptimal behaviors. Finally, the relationship between negative beliefs and rates of exposure utilization, calculated as a percentage of sessions with and without exposure delivery, will be assessed using correlational analyses consistent with past training trials incorporating the EPCS coding system [(54, 55); Hypothesis 4].

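### Hypotheses 3 and 4 relate delivery to post-training TBES with no arm term, so the association cannot separate belief change from arm-specific supervision and practice

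*Protocol article*

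**What the plan says.** The Hypothesis 3 analysis is given under Anticipated results. Its model is a regression on beliefs: "in-session behavior will be examined as a function of post-training TBES scores using GLM (Gaussian distribution"), with separate tests for optimal and suboptimal behaviours. The unit of analysis is the therapist, since "Rates of optimal and suboptimal delivery behaviors will be calculated for each therapist with recorded session data". For Hypothesis 4, the relation between negative beliefs and the percentage of sessions with exposure "will be assessed using correlational analyses consistent with past training trials incorporating the EPCS coding system". Post-training TBES is the only predictor named for Hypothesis 3, and no adjustment or split by arm is named for either hypothesis. In the same section arm is named for Hypothesis 1, where "group status (E2E vs. didactic) will be entered as a predictor of post-workshop total TBES score".

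Supervision ran during the phase in which delivery is recorded. Therapists "attended weekly (60-min), condition-specific consultation meetings". According to the Supervision section, didactic meetings "avoided conversation about therapist anxiety and the E2E concept", whereas E2E meetings "had a similar focus on delivery principles and troubleshooting but also prioritized each therapists’ processing of negative beliefs". The section adds: "Specifically, therapists were asked what negative beliefs they planned to test in their upcoming exposure sessions", and says that therapists reflected on the result at the next meeting. The section on the E2E condition says that these therapists also completed partner exposures, taking turns as patient and therapist.

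**The concern.** Hypothesis 1 expects arm to move the predictor, post-workshop TBES. Two other parts of the E2E package can move the outcome without acting through that predictor. One is weekly belief-focused supervision, which comes after workshop TBES has been measured. The other is workshop practice at directing someone else's exposure. Arm is then a common cause of predictor and outcome, and the stated analyses leave it out. Any arm difference in delivery would be credited to workshop belief change.

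This bears on a stated primary goal, which is to show that change in the beliefs target goes with in-session delivery. The Summary also presents the procedures as isolating the mechanism by which E2E affects practice. An unadjusted association can look like that mechanism even when lower beliefs do not go with better delivery inside either arm.

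**Working it through.** The article gives no sample size, power, alpha or effect size for Hypotheses 3 and 4, so there is no planned figure to reproduce. The check asks how large an association arm alone would create.

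**Inputs from the article**
- Therapists trained in Phase 2: 36 (Turnover). This is the upper limit for a one-rate-per-therapist analysis.
- Share of trained therapists who left: 57% (Turnover). 36 × 0.43 = 15.5, so about 15 stayed.
- Patients recruited to date: 21 (Patient participants). Each therapist was encouraged to refer one or two, so at most 21 therapists have session data to date, and perhaps fewer.

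**Assumptions, none given in the article**
- Equal arms (p = 0.5), two-sided alpha 0.05, and post-training TBES read as the end-of-workshop score.
- d1 is the arm difference in TBES and d2 is the arm difference in delivery that bypasses TBES, both in within-arm SDs.
- There is no association between TBES and delivery within either arm.

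**Induced correlation**

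|rho| = p(1−p)·d1·d2 / √[(1 + p(1−p)·d1²)(1 + p(1−p)·d2²)]

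With p = 0.5 and d1 = d2 = d this is (d²/4)/(1 + d²/4):
- d = 0.5: 0.0625/1.0625 = 0.06
- d = 0.8: 0.16/1.16 = 0.14
- d = 1.0: 0.25/1.25 = 0.20
- d = 1.5: 0.5625/1.5625 = 0.36

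**Rejection rate of the unadjusted test**

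By Fisher z, the statistic is centred at atanh(rho)·√(n−3). At n = 21 and d = 0.8 the centre is 0.139 × 4.243 = 0.589. The two tails are P(Z > 1.371) + P(Z < −2.549) = 0.085 + 0.005, or about 9%. The simulation used 20,000 runs per setting.

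| d1 = d2 | rho | Fisher z, n = 21 | Simulated, n = 15 | Simulated, n = 21 | Simulated, n = 36 |
|---|---|---|---|---|---|
| 0.5 | 0.06 | 6% | 5.5% | 5.9% | 6.6% |
| 0.8 | 0.14 | 9% | 7.9% | 9.5% | 12.6% |
| 1.0 | 0.20 | 14% | not run | not run | not run |
| 1.5 | 0.36 | 36% | 28.4% | 40.4% | 62.7% |

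With d1 = 0 and d2 = 0.8, the rate is 5.0–5.2% at all three sizes: if E2E does not shift TBES there is no bias. With arm in the model, the mean partial correlation is about zero and the rate is 4.8–5.4% in every setting.

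**Price of the arm term**

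Arm explains a share R² = (d1²/4)/(1 + d1²/4) of TBES. With residual variance held fixed, the variance of the TBES coefficient is multiplied by 1/(1−R²) = 1 + d1²/4. This is 1.06, 1.16, 1.25 and 1.56 for the four values of d. At 1.5 SD the standard error rises by √1.56 = 1.25. Baseline TBES adds to this, by an amount the documents do not allow one to calculate.

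**The case against.** The strongest objection is that arm-induced belief change is part of the mechanism the trial wants to show. An arm term removes that variation together with the bias and leaves a within-arm association, which is itself not randomised. The unadjusted analysis does answer the question as worded, namely whether beliefs and delivery are associated. This stands. It is a reason to keep the unadjusted estimate beside the adjusted one, but not to rely on it alone, because it cannot tell the intended path from supervision.

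Second, the trial is a pilot. The Discussion says its assumptions are to be met initially and confirmed in a larger trial. That limits what is claimed, but the caveat concerns power and does not remove confounding.

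Third, the Supervision section says that duration and frequency were equal and that belief discussion took little extra time. That argues against assuming a large direct effect on delivery, and nothing in the article supports 1.0–1.5 SD. The smaller cases deserve equal weight.

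Fourth, an analysis plan not shown could add covariates. This is possible, but the article states a model with its predictor and names arm only where Hypothesis 1 uses it. The point is about the analysis as stated.

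A reader might also infer that no randomised comparison of delivery or utilization is planned at all. The documents do not establish that. The article is condensed, and the figure said to show the pathways for testing the hypotheses is not available. One can say only that the text shown names no such comparison.

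**Conclusion.** The point holds as a should-fix. As stated, the Hypothesis 3 and 4 analyses omit a variable that the design makes a likely common cause of beliefs and delivery, so the unadjusted association cannot separate belief change from other E2E components.

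Bias requires both an arm effect on TBES and an arm effect on delivery that bypasses TBES. Under the assumptions above it ranges from negligible at 0.5 SD to serious at 1.5 SD, and it grows with the success of Hypothesis 1. If E2E supervision or practice improves delivery, its direction favours the trial's hypothesis.

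A reader might go further and conclude that a positive association would be an artefact of supervision. The documents do not support that: they show that the route exists, not that it operates or how large it is.

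**What to change.** - Report the Hypothesis 3 and 4 associations twice: without arm, and with arm and baseline TBES in the model. Base any statement about mechanism on the adjusted, within-arm estimate.
- State that delivery was measured under arm-specific supervision.
- Report the randomised arm difference in optimal rate, suboptimal rate and utilization with 95% confidence intervals. Label it as the combined effect of E2E workshop and E2E supervision among therapists with session data, since turnover and referral decide who contributes.

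No new data are needed. Adding arm and baseline TBES costs up to two degrees of freedom: with 21 therapists, the residual falls from 19 to 17. The interval for the TBES coefficient widens, with variance up by a factor of about 1.56 from arm alone at a 1.5 SD arm difference. The arm term does not remove within-arm confounding, for example by knowledge or self-efficacy, or selection through turnover, and the report should say so.
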